#### Pregnancy Test Results

A negative urine pregnancy test (women of childbearing potential only) will also be required the morning of dosing prior to drug administration. The Study Physician will be notified of urine pregnancy test results. A positive pregnancy test will result in the dose being canceled with no option for future rescheduling. The patient will be withdrawn from the study.

#### Pre-Dose Cardiovascular Monitoring

**Table 2:** Pre-Dose Blood Pressure Monitoring

| Cardiovascular Monitoring (Blood Pressure): Pre-Dose                                                                                                                                                 |            |                                                                                                                                                |
|-------------------------------------------------------------------------------------------------------------------------------------------------------------------------------------------------------------|------------|------------------------------------------------------------------------------------------------------------------------------------------------|
| Blood pressure will be obtained prior to dose administration  . Blood pressure assessments will be conducted by trained study personnel. The following safety parameters have been established: |            |                                                                                                                                                |
| Result                                                                                                                                                                                               |            | Instructions                                                                                                                            |
| SBP < 140 mmHg and DBP < 90 mmHg                                                                                                                                                                            | Acceptable | Proceed with dosing                                                                                                                            |
| SBP ≥ 140 mmHg or DBP ≥ 90 mmHg                                                                                                                                                                             | High       | Wait a minimum of 5 minutes and repeat blood pressure to determine if elevation is temporary. Participant should continue to remain recumbent. |
|                                                                                                                                                                                                             |            | If repeat BP is < 140 mmHg and < 90 mmHg, proceed with dosing                                                                                  |
|                                                                                                                                                                                                             |            | If three readings are elevated  , consult with the study physician for further evaluation and follow up.                           |

The initial reading should occur after the participant has been recumbent a minimum of 10 minutes

Dosing may be rescheduled at the discretion of the site PI or study physician. If > 7 days have elapsed since the Baseline visit, all Baseline measures must be repeated before dosing. If > 40 days have elapsed since the original Screening date the participant will be unable to participate in the study.

#### 9.3.2 Dosing

Following successful completion and acceptable results of the above scheduled assessments the participant will be dosed. When the participant is ready, he or she will receive a single dose of the study drug (25 mg psilocybin or 100 mg niacin placebo), administered as a capsule and taken with approximately 200 ml of water. Regardless of the study drug received, the participant will be under observation for at least 7 hours following ingestion.

Following study drug ingestion, it is recommended that study staff entering the session room be limited to the two Facilitators. Only in the event of an emergency should additional study staff enter the room. The rationale for minimizing who enters the session room is to reduce distractions for the participant.

#### Session Facilitators

Facilitators will be licensed psychologists with experience in the psychological treatment of MDD. Both Lead and Co-Facilitators will have adequate training to identify safety issues during the participant's preparation, dosing, and integration sessions, and will have undergone specific Clinical Facilitator training.

For the majority of the dosing session, both Facilitators will be present in the session room and will attend to the participant. At least one Facilitator will always be present in the session room to continuously observe and evaluate the participant's physical and mental status (allowing for infrequent, short breaks; e.g. facilitator bathroom breaks). Continuous supervision provides a safety structure and ensures that the participant will receive reassurance and emotional support from the Facilitators; should he/she experience strong emotions or become anxious or agitated during the session. Specific dosing session safety monitoring, via eCRF, will be conducted at regular, pre-specified times through assessment of the following: nausea, acute physical or psychological distress, including self-harm, and self-reported anxiety. This is intended to provide Facilitators with an enhanced ability to monitor participant safety and communicate any observed symptoms to the Study Physician, who will determine if immediate clinical assessment is warranted.

#### Role of the Study Physician During Dosing

The on-call Study Physician is responsible for the overall safety of participants, and he/she will oversee the medical management of study participants during the dosing session, as needed.

- Availability during Dosing: The Study Physician will be on-call throughout the duration of the dosing session and the Study Physician or a psychiatry MD will need to be available to be onsite within approximately 5 minutes in the event of an emergency for medical/psychiatric assessment. An MD is responsible for administering rescue medications, should these be warranted.
- End of Dosing Day: The Study Physician or a designated study nurse will assess the participant in-person at the end of the dosing day to determine if he/she is ready to be released from the research site.
- Overnight: In case of need for support during the night the patient will be referred to the emergency ward of the Norra Stockholms Psykiatri (open 24/7/365). The Study Physician will be on-call following participant release and until the following morning when the participant returns for his/her integration session.

#### Rescue Medications Available During Dosing

In the unlikely event that a participant requires medication management for blood pressure, anxiety or psychosis, the study physician may use the eg the following medications per his/her medical discretion:

1. Nitroglycerin
2. Clonidine
3. Diazepam or oxazepam
4. Risperidone

The use of rescue medications to control symptoms will be at the judgment of the treating physician, therefore use of specific medications is not protocolized. The study site will supply the rescue medications, directly or via the medical emergency unit, Capio S:t Görans Hospital which is at the same hospital area as the study site. The date and time of medication administration, reason for administration, as well as the name and dosage regimen of the rescue medication must be recorded on the Concomitant Medications log. Use of psychotropic agents (e.g. diazepam, risperidone) will be on a single dose/time limited basis and hence will not fall under the study exclusionary criteria regarding chronic use of these agents prior to enrollment.

In the unlikely event of a medical or psychiatric emergency that cannot be safely managed by staff with reassurance or pharmacological intervention, the study physician will determine if the participant will be needed to receive treatment via the psychiatric emergency unit at the hospital area. If necessary, this treatment can be given according to the Swedish law regarding compulsory psychiatric treatment, *Lagen om Psykiatrisk Tvångsvård*.

#### Cardiovascular Monitoring During Dosing Session

Blood pressure and heart rate will be obtained at 30, 60, 90, 120 minutes, 4, 6, and 7 hours after drug administration. Participants will not be discharged until after the 7-hour blood pressure and heart rate assessments have been completed. Measurements must be collected within +/-10 minutes of the scheduled time point. Measurements will be conducted by trained study personnel. Blood pressure measurements should occur after the participant has been recumbent a minimum of 10 minutes.

**Table 3:** Blood Pressure Monitoring during Dosing

| Cardiovascular Monitoring (Blood Pressure): Dosing Session                            |                                                                                                                                    |
|----------------------------------------------------------------------------------------------|------------------------------------------------------------------------------------------------------------------------------------|
| The following Blood Pressure safety parameters have been established for the dosing session: |                                                                                                                                    |
| Result                                                                                | Instructions                                                                                                                |
| SBP $\leq$ 170 mmHg and DBP $\leq$ 95 mmHg                                                   | No additional follow up needed, take BP at next scheduled time point.                                                              |
| SBP $>$ 170 and $<$ 200 mmHg or DBP $>$ 95 and $<$ 110 mmHg                                  | Repeat every 5 minutes for a total of three readings over 15 minutes.
• If three or more readings are elevated consult with the |

|                                               |                                                                                                                                                                                                                                                                                                                                                                                                                                                                                                                                                                                                                                                                                                                                                                                                                                                                                                                                                                                                                                                                                                                                                                                                          |
|-----------------------------------------------|----------------------------------------------------------------------------------------------------------------------------------------------------------------------------------------------------------------------------------------------------------------------------------------------------------------------------------------------------------------------------------------------------------------------------------------------------------------------------------------------------------------------------------------------------------------------------------------------------------------------------------------------------------------------------------------------------------------------------------------------------------------------------------------------------------------------------------------------------------------------------------------------------------------------------------------------------------------------------------------------------------------------------------------------------------------------------------------------------------------------------------------------------------------------------------------------------------|
| SBP $\geq$ 200 mmHg or
DBP $\geq$ 110 mmHg | 
Consult with the study physician for further evaluation and follow up. Medication and medication administration is at the clinical judgment of the Study Physician and is not protocolized. The following medication administration is a recommendation; however, the Study Physician may treat the participant based on his or her own judgement and with the medications available on site.
 
 
• The participant may be treated with sublingual nitroglycerin 0.4 mg
 
• If blood pressure readings do not decrease below these thresholds after 5 minutes, the same dose of nitroglycerin will be administered
 
• A third dose of nitroglycerin will be given after another 5 minutes, if readings remain elevated above these levels (maximum dose is 0.4 mg x 3)
 
• If blood pressure remains <math>\geq</math>200 systolic or <math>\geq</math>110 diastolic, at the judgment of the study physician, the participant will be treated with oral clonidine (e.g., 0.1 mg) and the Study Physician will evaluate whether transport to the emergency room is necessary..
 
 |
|-----------------------------------------------|----------------------------------------------------------------------------------------------------------------------------------------------------------------------------------------------------------------------------------------------------------------------------------------------------------------------------------------------------------------------------------------------------------------------------------------------------------------------------------------------------------------------------------------------------------------------------------------------------------------------------------------------------------------------------------------------------------------------------------------------------------------------------------------------------------------------------------------------------------------------------------------------------------------------------------------------------------------------------------------------------------------------------------------------------------------------------------------------------------------------------------------------------------------------------------------------------------|

 Administration of any medications must be recorded on the Concomitant Medications form

**Table 4:** Heart Rate Monitoring during Dosing

| Cardiovascular Monitoring (Heart Rate): Dosing Session                            |                                                                                                                                                                                                   |
|------------------------------------------------------------------------------------------|---------------------------------------------------------------------------------------------------------------------------------------------------------------------------------------------------|
| The following Heart Rate safety parameters have been established for the dosing session: |                                                                                                                                                                                                   |
| Result                                                                            | Instructions                                                                                                                                                                               |
| < 50 BPM                                                                                 | Repeat every 5 minutes for a total of 3 readings over 15 minutes. 
 
• If three or more readings are below 50 BPM consult with the study physician
 
 |
| $\geq$ 50 BPM and $\leq$ 110                                                             | No additional follow up needed, take HR at next scheduled time                                                                                                                                    |
| > 110 BPM                                                                                | Repeat every 5 minutes for a total of three readings over 15 minutes 
 
• If three or more readings are elevated consult with the study physician
 
  |

The final scheduled vital signs assessment is at 7-hours post-dosing, with the following safety parameters/ instructions.

| The following safety parameters have been established for the End of Dosing Day (7-hour) blood pressure (BP) and heart rate (HR) measurements  . |                  |                                                    |
|--------------------------------------------------------------------------------------------------------------------------------------------------------------|------------------|----------------------------------------------------|
| BP Result                                                                                                                                             | HR Result | Instructions                                |
| SBP < 140 mmHg and
DBP < 90 mmHg                                                                                                                          | < 100 BPM        | No action needed. The participant may be released. |

|                                              |                |                                                                                                                                                                                                                                                                                                                                                                                                                                                                                                                                                                                                                                                                                                                                                                                                                                                                                                                                                                                                                                                                                                            |
|----------------------------------------------|----------------|------------------------------------------------------------------------------------------------------------------------------------------------------------------------------------------------------------------------------------------------------------------------------------------------------------------------------------------------------------------------------------------------------------------------------------------------------------------------------------------------------------------------------------------------------------------------------------------------------------------------------------------------------------------------------------------------------------------------------------------------------------------------------------------------------------------------------------------------------------------------------------------------------------------------------------------------------------------------------------------------------------------------------------------------------------------------------------------------------------|
| SBP $\geq$ 140 mmHg or
DBP $\geq$ 90 mmHg | $\geq$ 100 BPM | Participant should continue to remain recumbent.
Wait a minimum of five minutes and repeat measurement to determine if elevation is temporary. The measurement can be repeated up to three times, separated by a minimum of five minutes, with the participant remaining recumbent. Document any additional measurements.                                                                                                                                                                                                                                                                                                                                                                                                                                                                                                                                                                                                                                                                                                                                                                               |
| SBP $\geq$ 140 mmHg or
DBP $\geq$ 90 mmHg | $\geq$ 100 BP  | 
If there are three consecutive readings of SBP <math>\geq</math> 140 mmHg or DBP <math>\geq</math> 90 mmHg, contact the Study Physician for further in-person evaluation and follow-up.
 
 
• The participant may be released if the Study Physician does not feel the elevated measurement is concerning.
 
• If the Study Physician feels the elevation is concerning, the participant will remain on site for further evaluation. If the Study Physician feels medication administration is warranted, he/she can treat the participant with medications available at the site.
 
• If the participant responds to either waiting or medication administration, and the measurement decreases to a level the Study Physician does not feel is concerning, the participant may be released.
 
• If the participant does not respond and the Study Physician feels the elevation is concerning and warrants further evaluation, Study Physician will evaluate whether transport to the emergency room is necessary.
 
 |

Heart rate and blood pressure measurements should occur after the participant has been recumbent a minimum of 10 minutes

Administration of any medications must be recorded on the Concomitant Medications form

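### The 7-hour discharge table conflicts with Table 4 on heart rate: its release row has no lower limit, and its physician-contact sentence leaves heart rate out

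*Protocol*

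**What the plan says.** All the rules are in Protocol section 9.3.2, under Cardiovascular Monitoring During Dosing Session. Blood pressure and heart rate are taken at 30, 60, 90 and 120 minutes and at 4, 6 and 7 hours.

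**Table 4** opens with "The following Heart Rate safety parameters have been established for the dosing session" and has three rows:
- Below 50 BPM: repeat readings, then "If three or more readings are below 50 BPM consult with the study physician".
- 50 to 110 BPM: "No additional follow up needed, take HR at next scheduled time".
- Above 110 BPM: repeat readings, then "If three or more readings are elevated consult with the study physician".

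**The 7-hour table** follows, introduced by "The final scheduled vital signs assessment is at 7-hours post-dosing, with the following safety parameters/ instructions". It also has three rows:
- SBP below 140, DBP below 90 and heart rate below 100: "No action needed. The participant may be released".
- SBP of 140 or more or DBP of 90 or more, with a heart rate of 100 or more in the next column: "Wait a minimum of five minutes and repeat measurement to determine if elevation is temporary", up to three times.
- The same blood-pressure cell, again with 100 or more in the heart-rate column (the unit is printed as BP). The instruction to contact the Study Physician begins "If there are three consecutive readings of SBP" and goes on to the 140 and 90 limits. It does not name heart rate.

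**The concern.** The two tables give different instructions for the same patient at two points.

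1. **Low heart rate.** Table 4 acts on a rate under 50. The 7-hour release row accepts any rate under 100, so a rate that calls for repeats and possibly a consult at 6 hours needs no action at 7 hours.
2. **High heart rate.** The last row of the 7-hour table includes a rate of 100 or more as a condition, but the sentence that sends the case to the physician depends on blood pressure alone. Persistent tachycardia with normal blood pressure leads to repeat readings and then to no stated contact, although Table 4 sends a persistent rate above 110 to the physician.

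This is the last scheduled measurement before discharge. Section 17.1.1 lists increased heart rate among the commonly reported effects of psilocybin. Section 18.1.1 counts a rate above 100, and a clinically significant fall in heart rate, as adverse events. At stake is whether staff at the end of the dosing day know when they must call the physician.

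**Working it through.** No sample-size, power or error-rate figure is involved, so the check is to trace both sets of rules on the same readings. Blood pressure is held below 140/90 throughout, so that only heart rate varies. The cut-points in the two tables (50, 100 and 110) give four bands.

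| Heart rate (BPM) | Table 4 | 7-hour table as worded | Comparison |
|---|---|---|---|
| < 50 | Repeat; consult after three | No action; may be released | Consult missing |
| 50 to 99 | No follow-up | No action; may be released | Same |
| 100 to 110 | No follow-up | Repeat | 7-hour table stricter |
| > 110 | Repeat; consult after three | Repeat; contact sentence not triggered | Consult missing |

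The result is 1 band the same, 1 stricter and 2 of 4 without the physician consult.

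**Example 1.** 118/76 with a heart rate of 45 on three readings. At 6 hours, Table 4 requires a consult. At 7 hours, 118 < 140, 76 < 90 and 45 < 100, so the release row is met.

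**Example 2.** 120/80 with a heart rate of 125 on three readings. At 6 hours, 125 > 110 and Table 4 requires a consult. At 7 hours, 125 ≥ 100, so the release row is not met and readings are repeated. The contact sentence needs SBP ≥ 140 or DBP ≥ 90 on three consecutive readings; 120 and 80 never meet it.

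**Does Table 4 also apply at 7 hours?** The list of reading times includes 7 hours, so it may.
- If the 7-hour table replaces Table 4, both gaps stand.
- If both tables apply, example 2 reaches the physician through Table 4. Example 1 then has two conflicting instructions: repeat and consult, or do nothing.

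**How do the two columns join?** The table does not say whether the blood-pressure and heart-rate cells in its second and third rows combine as *and* or as *or*. The trace above assumes that a high heart rate alone is enough for the repeat row. If both conditions were required, isolated tachycardia would fit no row of the table.

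**The case against.** Four points can be made for the table as it stands.

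- **A tachycardic patient is not told to go home.** A rate of 100 or more fails the release row, and the only release routes in the last row pass through the Study Physician's judgement. The bullets there refer to an elevated measurement in general terms, so heart rate was probably meant to count. This stands as a reading of intent, and it limits the second point to a missing contact trigger. But the bullets take effect only once the physician is involved, and the sentence that involves the physician omits heart rate.
- **Nobody leaves on the table alone.** Section 9.3.3 requires apparent return to the baseline physiological state and a release assessment by the Lead Facilitator and the Study Physician or designee. Section 9.3.2 also requires an in-person assessment by the physician or a designated nurse, with a physician on call. This lowers the risk. But the assessor need not be a physician, and neither section gives a heart-rate limit or a rule for calling.
- **High heart rate is already an adverse event.** Section 18.1.1 covers rates above 100, and section 18.4 makes the PI responsible for managing all adverse events. True, but neither sets any timing relative to discharge.
- **A low rate may already have been caught, and release is only permitted.** Persistent bradycardia at 6 hours would have reached the physician under Table 4, and staff applying both tables could consult before releasing. That leaves mainly a fall in rate after 6 hours. The protocol also does not describe slowing of the heart as an expected effect of psilocybin. This reduces the likely frequency, but the release row still says that nothing need be done at a rate on which Table 4 acts.

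**Conclusion.** The concern holds on both points. The release row contradicts the protocol's own lower limit of 50, and the contact sentence does not cover the heart-rate condition in its own row. With blood pressure below 140/90, the physician consult that Table 4 requires is absent from the 7-hour table in two of four heart-rate bands.

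The count rests on two assumptions: that the 7-hour table is applied as worded, and that a high heart rate alone triggers its repeat row. If Table 4 also governs the 7-hour reading, the consult above 110 is restored and the conflict below 50 remains. No reading of the text removes both problems.

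This is a drafting fault in a discharge-safety rule, partly offset by clinical checks elsewhere. It has no bearing on the endpoints, sample size, randomization or analysis. It should be corrected.

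**What to change.** In the 7-hour table of section 9.3.2:

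1. Set the heart-rate condition for release to at least 50 and below 100 BPM, or to other limits the sponsor chooses and states.
2. State that an abnormal blood pressure or an abnormal heart rate each leads, by itself, to repeat readings.
3. Add a heart rate of 100 or more, or below 50, to the three-consecutive-readings sentence that sends the case to the Study Physician, and correct the unit in that row to BPM.
4. Say in one line whether Table 4 still applies to the 7-hour reading.

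The readings are already taken, so nothing new is measured. The cost is an occasional extra physician call at the end of the dosing day, for example for a patient whose usual resting rate is below 50.
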